### Statistical analysis

All analysis and data visualization will be performed using IBM SPSS (Version 25.0), R (Version 4.1.1).

Baseline data will be displayed using descriptive statistics (eg, means, SD, median, IQR, proportions). We will test the group balance achieved by randomization through appropriate statistical tests (eg, Student’s t tests, Pearson’s χ^2^ tests). Outcomes with a continuous distribution will be compared between groups using the mean (Student’s t test) and Pearson’s χ^2^ test will be used for binary categorical data where categorical variables are expressed as frequencies and percentages and continuous variables are expressed as means and SD.

Preliminary statistical analysis of the primary outcome data will be performed according to the intention-to-treat principle, and the changes in DAS28 will be compared between patients treated with Wangbi granule and Wangbi placebo, and report the rate of deep remission. Further, two-way repeated measures analysis of variance (ANOVA) will be used to examine any interaction effects of the outcome variables between the two groups at the four time points. Mauchly’s sphericity test will be used to examine the spherical assumptions of the repeated measures ANOVA. Bonferroni-corrected post hoc multiple comparisons will be used to examine simple effects between groups at different time points and at different time points for each group.

Sensitivity analysis will be an essential part of the statistical analysis process to complement the interpretation of the results. Depending on the specifics of the data, the full samples will be divided into subgroups based on information about additional drugs (e.g. NSAIDs), co-existing underlying conditions (e.g. hypertension, diabetes), long-term use of other drugs, etc. The calculations will be re-run in each subgroup to verify the validity of the results. When necessary, a per protocol set (PPS) analysis will be part of the sensitivity analysis. If any variable has no more than 20% missing values, the MICE package in R will be used for multiple interpolation to replace it. For the statistical process, *P* < 0.05 is considered statistically significant.

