### Outcomes

The efficacy of Wangbi granule will be observed and the main outcome is DAS28 [19], assessed by a dedicated rheumatologist (associate senior physician or better). The changes in the DAS28 score will be recorded during the observation period. Moreover, participants are considered to have achieved deep clinical remission when the calculated DAS28 score is lower than 2.6.

Secondary outcomes include patient-reported outcomes (symptom score) [18], ACR50 [20], fatigue scale-14 (FS-14) [21], visual analogue scale for pain (VAS) [22], health assessment questionnaire disability index (HAQ-DI) [23] and biological markers [24] such as CRP and ESR. Specific secondary outcomes are shown in Table 3.

**Table 3 Tab3:** Secondary outcomes of the trial

Secondary outcomes	
ACR50	ACR response was used to evaluate improvement in RA. ACR response requires the collection of the degree of improvement in the number of joints with pressure pain and the degree of improvement in the number of joints with swelling and the degree of improvement in 3 of the following 5 items: patient’s assessment of pain, patient’s overall assessment of disease activity, physician’s overall assessment of disease activity, patient’s assessment of physical function (HAQ), and values of acute phase reactants (ESR, CRP). Percentage improvement in each indicator = (pre-treatment value − post-treatment value)/pre-treatment value * 100% ACR20: ≥ 20% improvement in joint pain and swelling, and ≥ 20% improvement in at least 3 of the other 5 items ACR50: ≥ 50% improvement in joint pain and swelling, and ≥ 50% improvement in at least 3 of the other 5 items ACR70: ≥ 70% improvement in joint pain and swelling, and ≥ 70% improvement in at least 3 of the other 5 items
VAS	Patients’ joint pain levels were evaluated using the VAS, expressed on a ten-point scale, with higher scores indicating more intense pain Face-to-face or telephone follow-ups were conducted at baseline, 4 weeks, 8 weeks, and 12 weeks of treatment, and patients were scored based on their subjective perceptions

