FS-14	FS-14 is used to measure the patient’s fatigue level. FS-14 was divided into 2 dimensions: physical fatigue (8 items) and mental fatigue (6 items). The scoring method is based on a 2-point scale, with 0 points for “No” and 1 point for “Yes”, and reverse scoring for items 10, 13 and 14, with a total score of 0 to 14 points, with higher scores representing heavier fatigue Face-to-face or telephone follow-ups were conducted at baseline, 4 weeks, 8 weeks, and 12 weeks of treatment, and patients were scored based on their subjective perceptions
HAQ-DI	The HAQ-DI was used to assess the overall functional status of the patients. The questionnaire consists of 20 questions containing 8 areas of daily activity, with higher scores on each question representing poorer functioning Face-to-face or telephone follow-ups were conducted at baseline, 4 weeks, 8 weeks, and 12 weeks of treatment, and patients were scored based on their subjective perceptions
Symptom score	The patient’s symptoms associated with RA were recorded, including joint swelling, pressure pain, activity level, diet, etc. The greater the degree of performance of each symptom, the higher the score Face-to-face or telephone follow-ups were conducted at baseline, 4 weeks, 8 weeks, and 12 weeks of treatment, and patients were scored based on their subjective perceptions
Biological markers	All patients will have their venous blood and other required specimens collected on an empty stomach in the early morning of the specified date and tested in the testing department of each research center, and the biological samples will be frozen in a special refrigerator in China-Japan Friendship Hospital Routine blood, urine, and stool tests were performed at baseline, 4 weeks, and 12 weeks of the trial Electrocardiograph, ALT, AST, and serum creatinine were tested at baseline, 4 weeks, and 12 weeks of the trial to monitor the safety of drug administration ESR and CRP were measured at baseline and 12 weeks of the trial to monitor inflammation levels RF and ACPA were tested during the baseline period of the trial to determine the patient’s antibody levels Additional blood samples were collected at baseline, week 12 of the trial and used to test for various proteins and genes such as inflammatory cytokines

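### CRP, ESR and cytokine levels are to be compared by an unadjusted t test on means, with no allowance for skewness and no use of the baseline value; if the markers are strongly skewed and the effect is proportional, this can cost substantial power

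*Protocol article*

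**What the plan says.** The Statistical analysis section of the protocol article states, without condition: "Outcomes with a continuous distribution will be compared between groups using the mean", naming Student's t test. The same sentence adds that "continuous variables are expressed as means and SD". Median and IQR are offered only for describing baseline data. For the outcome comparison no transformation, rank test, check of shape or covariate is named. The significance rule is P "< 0.05 is considered statistically significant".

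The Outcomes section lists "biological markers [24] such as CRP and ESR" among the secondary outcomes. Table 3 says of timing that "ESR and CRP were measured at baseline and 12 weeks of the trial to monitor inflammation levels"; Table 4 adds a week-4 measurement, a discrepancy to be settled separately. Table 3 also lists blood samples taken at baseline and week 12, "used to test for various proteins and genes such as inflammatory cytokines".

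The section's other outcome model is a repeated-measures ANOVA over four time points. The markers are measured at two or three visits, so the t test is the only stated comparison that fits them.

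**The concern.** CRP, ESR and cytokine levels are positive quantities that may well be right-skewed. On the raw scale a few high values can then dominate both the mean and the SD. The t test keeps roughly its nominal error rate but becomes less sensitive to a proportional effect, and mean with SD describes such data poorly. In addition, an unadjusted comparison of final values discards the baseline measurement, which the trial collects anyway.

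At stake is the reading of the secondary and exploratory inflammation results. The Background cites anti-inflammatory action as part of the rationale, and the Discussion presents the blood inflammatory factors as a further aim. A true reduction in a marker could be reported as no difference because of the scale chosen.

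**Working it through.** **Inputs from the article.** Evaluable patients per arm: 155 (Sample size calculation). Significance level: 0.05, taken as two-sided. Method: Student's t test on means. The article gives no mean, SD, skewness, expected effect or power for any marker, so there is no figure of its own to reproduce.

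**Assumptions.** Log-normal values with SD *s* on the natural-log scale; a constant ratio of 0.7 (30% reduction); baseline to week-12 correlation 0.5. The article does not say whether final values or changes are compared for the markers, so both are shown.

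**Closed-form check at s = 1.0.**
- Log final values: z = ln(1/0.7) / (s·√(2/155)) − 1.96 = 0.357/0.1136 − 1.96 = 1.18, power 88%.
- Log ANCOVA: the standard error is multiplied by √(1 − 0.5²) = 0.866, so z = 3.140/0.866 − 1.96 = 1.67, power 95%.
- Raw final values: z = 0.3 / √[(e^(s²) − 1)(1 + 0.7²)/155] − 1.96 = 0.3/0.1285 − 1.96 = 0.37, power 65%. This normal approximation is somewhat low under skewness; simulation gives 67–70%.

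**Simulated power (4,000 runs per setting; repeat runs agree to within about 3 points).**

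| log-SD | raw final | raw change | log final | log ANCOVA |
|---|---|---|---|---|
| 0.8 | 91% | 80% | 97% | over 99% |
| 1.0 | 70% | 53% | 88% | 95% |
| 1.2 | 47% | 32% | 75% | 86% |

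Raw against log final values, the loss is 97 − 91 = 6 points at 0.8, about 20 at 1.0 (88 minus 67 to 70, that is 18 to 21) and 75 − 47 = 28 at 1.2. At 0.6 both tests are near 100% and nothing material is lost. The last column also contains the gain from baseline adjustment, which is a separate matter from skewness: 95 − 88 = 7 points at 1.0 and 86 − 75 = 11 at 1.2. Type I error was 4–6% for every method.

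**Same comparison away from the ceiling.** The near-100% figures at low log-SD partly reflect the size of the assumed effect. If the effect is instead set so that the log-scale t test has 80% power, the raw t test on final values has 78%, 75%, 69%, 67%, 60%, 52% and 41% at log-SD 0.3, 0.5, 0.7, 0.8, 1.0, 1.2 and 1.5. The small-effect relative efficiency s²/(e^(s²) − 1) is 0.88 at 0.5, 0.71 at 0.8 and 0.58 at 1.0. For raw against log change, raw power is 68–69% at 0.5, 54–55% at 0.8 and 42–46% at 1.0, for correlations of 0.3 to 0.7.

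**Description.** The raw SD divided by the mean is √(e^(s²) − 1): 1.3 at s = 1.0 and 1.8 at s = 1.2.

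**Counter-case.** Suppose treatment only pulls the top quarter of values down to its lower bound and leaves the rest unchanged. The raw t test then has 78%, 88%, 94% and 96% power at log-SD 0.6, 0.8, 1.0 and 1.2, and the log t test about 30% throughout.

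**The case against.** The strongest reply is that the loss is conditional on quantities the article does not give. That stands. The log-SD may differ between CRP, ESR and individual cytokines, and entry at DAS28 2.6 to 3.2 on stable treatment may narrow the spread. The form of the effect matters as well: in the counter-case the ranking of the two scales reverses.

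Nor is the log scale without a price. The estimand becomes a ratio of geometric means, and values below the detection limit need a rule. With 40% of values below the limit and set to half of it (both assumed), log-scale power at log-SD 1.0 falls from 88% to about 81%.

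A reader might therefore infer either that the planned test loses much of its power on every marker, or that switching scale costs nothing. The article supports neither reading.

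It can also be said that a short article leaves transformations to the analysis plan, and that a t test on logged values is still a t test on means. This carries some weight, but the article does not stay silent. It fixes a method for all continuous outcomes and a mean-and-SD summary, whose plain reading is the untransformed scale. An analysis plan that transformed the markers would depart from the published rule.

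Finally, these are secondary and exploratory markers for which the article claims no power. That limits the weight of the point without removing it.

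**Conclusion.** The point holds in conditional form. The stated rule applies an unadjusted t test on means to CRP, ESR and any cytokine levels, with no allowance for skewness and no use of the baseline value. If the markers are right-skewed and the effect is roughly proportional, the loss in power is negligible to small for mild skewness, moderate at a log-SD of about 0.7 to 0.8 and substantial from about 1.0 upwards. Log-normal shape, log-SD, effect size and correlation are all assumed. If the effect is confined to the highest values, the raw scale may do better.

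Two further inferences should be resisted. The planned test is not invalid, since its type I error stays near or below 5%. The DAS28 conclusion is not touched, since the point concerns only the laboratory markers. This is a cheap and worthwhile improvement to secondary analyses.

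**What to change.** In the Statistical analysis section, add that CRP, ESR and cytokine levels are analysed on the natural-log scale by ANCOVA with the log baseline value as covariate, reported as ratios of geometric means with 95% confidence intervals, and described by median and IQR. State how values below the detection limit are handled. Keep the raw-scale comparison as a supportive analysis, which covers an effect concentrated in the high values. Leave the DAS28 analysis as it is.

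The cost is two or three sentences. No patients, samples or visits are added, because baseline and week-12 values are already collected. What changes is the estimand, now a ratio of geometric means, and the detection-limit rule must be fixed before unblinding.

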**Methods and analysis:**

Two parallel randomized, triple-blind, placebo-controlled trials will be conducted. In six study centers, 340 eligible RA patients will be recruited and randomly allocated to either the intervention group or the control group (in a 1:1 ratio). They will receive Wangbi granule or Wangbi placebo 12.0 g each time, three times a day for 12 weeks. The primary outcome is the disease activity score derivative for 28 joints (DAS28). Secondary outcomes are patient-reported outcomes, American College of Rheumatology 50% response criteria (ACR50), fatigue scale-14 (FS-14), visual analogue scale for pain (VAS), health assessment questionnaire disability index (HAQ-DI) and biomarkers such as C-reactive protein (CRP) and erythrocyte sedimentation rate (ESR).

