### Allocation and blinding

A central randomization system will be applied in this study, with an independent contract research organization (CRO) implementing the randomized assignment and drug dispensing in each subcenter. Participants will be randomized to either the intervention or control group, and stratified block group randomization will be used for participant randomization. In the random assignment process, participants are first allowed to enter the zone group and then are randomly allocated. The length of the zone group is set to 4, and the six permutations obtained are designated as AABB, ABAB, ABBA, BAAB, BABA, BBAA, with A and B representing the intervention or control group, whose exact meaning is known only to the designer. Subsequently, a string of random numbers is generated by SPSS software, and the allocation sequence is obtained by selecting numbers between 1 and 6 and arranging the district groups in the order of random numbers. Once each subcenter has determined the eligibility of participants and obtained the written consent to participate in the trial, a number will be requested from the randomization manager. The complete sequence of generated assignments is kept at the CRO, and the designer will place them in sequentially numbered sealed opaque envelopes and store them in a locked cabinet.

Researchers, participants and statistical analysts will be blinded to group assignment. After all cases are included, all clinical data will be entered into the database and verified, and the data will be locked after confirmation of accuracy. Groups A and B will be divided into two groups at the first unblinding, but it is not clear which group is the intervention group. After the statistical analysis, the results will be processed and the second unblinding will be carried out to find out whether group A and group B represent the intervention group or the control group. If a serious adverse event or unexpected adverse reaction occurs during the trial, the patient’s blinding status will be broken with the consent of the Principal Investigator (PI), and all such cases will be reported to the Clinical Research Ethics Committee of the China-Japan Friendship Hospital.

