### Sample size calculation

The study used superiority design approach. Due to the lack of clinical studies of methotrexate and tofacitinib in combination with Wangbi granule, we refer to the previous studies of methotrexate in combination with Wangbi granule for the treatment of RA [25]. In order to observe the deep remission effect of the Wangbi granule on RA condition, the final DAS28 score of the intervention group needs to be at least 0.5 points lower than that of the control group, so the cut-off value δ takes − 0.5. We adopted single-sided calculation whereα is 0.025, β is 0.2, and the sample size is 1:1, then the single group sample size of 155 cases is obtained. Considering a shedding rate of 10%, 170 cases are needed in each group, and the final total sample size is 340.According to the plan, as the lead center, China-Japan Friendship Hospital will complete the intake of 90 samples, and the remaining 5 centers will equally distribute the remaining 250 samples.

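### The DAS28 analysis leaves out the randomisation strata and a baseline covariate, and the plan does not fix which analysis, at which visit, decides the trial

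*Protocol article*

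**What the plan says.** **Outcome.** The abstract states: "The primary outcome is the disease activity score derivative for 28 joints (DAS28"). Neither there nor under Outcomes is a visit named as primary. Table 4 schedules DAS28 five times, from baseline (T0) to one month after treatment (T4).

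**Randomisation.** Under Allocation and blinding, "stratified block group randomization will be used for participant randomization", with blocks of four. The stratification factor is not named. Assignment is carried out for each subcenter, so centre is the likely one.

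**Sample size.** The trial is sized on the follow-up score: "the final DAS28 score of the intervention group needs to be at least 0.5 points lower than that of the control group".

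**Analysis.** Under Statistical analysis:
- The general rule for continuous data is "Outcomes with a continuous distribution will be compared between groups using the mean (Student’s t test"). Binary outcomes get a chi-square comparison. Neither has a covariate or stratum term.
- The intention-to-treat analysis of the primary outcome, described as preliminary, is that "the changes in DAS28 will be compared between patients treated with Wangbi granule and Wangbi placebo, and report the rate of deep remission".
- After that, "two-way repeated measures analysis of variance (ANOVA) will be used to examine any interaction effects" over four time points. Bonferroni correction applies to the post hoc comparisons within this ANOVA.
- One threshold, P < 0.05, covers the whole section.

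**The concern.** There are two separate issues.

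1. **Strata.** Stratified randomisation balances the arms on the stratum. If the stratum predicts outcome, the estimated difference varies less than an unadjusted t test assumes. The test is then conservative and gives away some power that a stratum term would recover.

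2. **No single deciding result.** DAS28 change, the remission rate and the group-by-time interaction all bear on the primary outcome. They are not ranked, and no visit is fixed for the first two. The variable used for sizing (final score) is not the variable tested (change). A reader of the final report could not tell whether the result presented as primary was the one intended, and a choice among three results at 5% each carries more than a 5% chance of a false positive.

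**Working it through.** **Step 1. The plan's own figure.** Inputs from Sample size calculation: difference 0.5, one-sided alpha 0.025, power 80%, 1:1 allocation, 155 per group. No SD is stated, so 155 cannot be reproduced directly. Solving n = 2(z₁ + z₂)²SD²/δ² for the SD:

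SD = √[155 × 0.25 / (2 × (1.960 + 0.842)²)] ≈ 1.57.

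An SD of 1.0 would give 63 per group and 1.2 would give 91, so 1.57 is used below as the value implied by the plan. One-sided 0.025 and two-sided 0.05 are the same criterion, so the two alpha statements do not conflict.

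**Step 2. What a baseline covariate adds to a change score.** The entry window of 2.6 to 3.2 is 0.6 wide. The baseline SD is 0.6/√12 = 0.173 if scores are uniform, and cannot exceed 0.30. With s_B = 0.173 and s_Y = 1.57:

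- Variance of change = s_Y² + s_B² − 2ρ s_Y s_B
- ANCOVA residual variance = s_Y²(1 − ρ²)

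| Assumed correlation ρ | Variance of change | ANCOVA variance | SE ratio, change/ANCOVA |
|---|---|---|---|
| 0 | 2.495 | 2.465 | 1.006 |
| 0.3 | 2.332 | 2.243 | 1.020 |
| 0.5 | 2.223 | 1.849 | 1.097 |

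The last row needs a regression slope of ρ s_Y/s_B = 4.5 DAS28 points per baseline point, which is hard to believe. A gain of 0 to 2% is the realistic range.

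**Step 3. What the stratum term adds.** If centre explains a fraction ICC of the variance, the unadjusted SE is too large by about 1/√(1 − ICC): 1.026, 1.054 and 1.118 at ICC 0.05, 0.10 and 0.20. A simulation of the planned design gives slightly smaller ratios. Its inputs:
- from the protocol: 340 patients; centres of 90 and five of 50; blocks of four
- assumed: centre as the stratum; baseline uniform on 2.6 to 3.2; SD 1.57; correlation 0.5 between successive follow-up visits; a slope of 1 on baseline, so the excess shown comes from centre and not from baseline.

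The expected type I error is 2[1 − Φ(1.96 × ratio)].

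| Assumed ICC | SE ratio, simulated | Type I error, formula | Type I error of t test, simulated | Type I error of ANCOVA, simulated |
|---|---|---|---|---|
| 0 | 1.00 | 0.050 | 0.051 | 0.050 |
| 0.05 | 1.02 | 0.046 | 0.043 | 0.050 |
| 0.10 | 1.04 | 0.041 | 0.044 | 0.051 |
| 0.20 | 1.10 | 0.032 | 0.031 | 0.045 |

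With 2,500 runs per row, the simulation error at 5% is √(0.05 × 0.95/2500) = 0.004. The two middle t-test values are therefore only about 1.5 errors below 0.05; the formula supports their direction. At a true difference of 0.5, power is 0.863 unadjusted and 0.885 adjusted at ICC 0.10, and 0.849 and 0.844 with no centre effect (equal within simulation error).

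**Step 4. Three routes.** In the same simulation with no treatment effect, each of t test on week-12 change, chi-square on remission (below 2.6) and ANOVA interaction (Greenhouse-Geisser corrected, T0 to T3) rejects about 5% of the time with no centre effect. At least one rejects with probability:
- 0.099 to 0.112 with no centre effect (SD 1.0 or 1.57, visit correlation 0.3 to 0.7)
- 0.092, 0.100 and 0.076 at ICC 0.05, 0.10 and 0.20.

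Three independent tests would give 1 − 0.95³ = 0.143; these fall below that because they share data.

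**Step 5. Final score against change.** Under randomisation both have the same expected group difference. At ρ = 0.3 the SD of change is √2.332 = 1.53, against 1.57 for the final score. The mismatch hardly affects the sample size, but the primary variable is still stated in two ways.

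**The case against.** The strongest reply is that the planned t test is valid. Ignoring strata makes it conservative, its power at the implied SD still exceeds the planned 80%, and covariate detail is often left to the analysis plan. The text also has an order: change first, then the ANOVA, then sensitivity analyses. Remission is only to be reported, so its chi-square test follows only from the general rule for binary data, and nowhere does the plan claim success on any one of three results. All of this stands. It limits the severity and makes the 8 to 11% conditional. It does not supply a deciding test or visit, and the text has already fixed tests without a stratum term.

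Four stronger readings are tempting, and the documents do not support them.

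- **That baseline is ignored.** The change score subtracts it, and it appears to be one of the four ANOVA time points, since Participant timeline counts four recordings from enrolment to week 12. What is absent is a baseline covariate.
- **That standard errors are too wide as a matter of fact.** That needs a prognostic stratum. The factor is unnamed and no centre effect is documented.
- **That patients with a missing visit are deleted.** Statistical analysis plans multiple imputation for variables with up to 20% missing, and Data management uses the last recording for those who withdraw.
- **That keeping baseline as an ANOVA level costs the interaction test much power.** With an equal 0.5 effect at every follow-up visit and SD 1.57, the simulated power is 0.852, against 0.849 for the t test. The plan also provides Mauchly's test of sphericity. Other effect patterns could give other figures, but the protocol states none.

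**Conclusion.** The point holds as a should-fix. The missing deciding analysis and visit, and the two versions of the primary variable, can be read directly from the text. If a win on any of the three analyses were claimed, the false-positive rate would be about 8 to 11% instead of 5%.

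Omitting the strata is a smaller matter of efficiency: about 2 to 10% in the standard error and a type I error of about 3 to 4.5% if centre is the stratum with an ICC of 0.05 to 0.20, and nothing if centre has no effect. The baseline covariate adds little because of the narrow entry window.

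The SD, visit correlations, ICC, uniform baseline and centre as stratum are all assumptions; the documents give none of them.

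**What to change.** Before unblinding, state the following.

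- **Primary test:** week-12 DAS28 in all randomised patients, by ANCOVA or by a mixed model for repeated measures over the post-baseline visits. Covariates are baseline DAS28 and the stratification factor(s) actually used, which should be named under Allocation and blinding. Test at two-sided 0.05 and report the difference with its 95% confidence interval. With baseline as a covariate, final score and change give the same treatment estimate, which also removes the mismatch with the sample size section.
- **Visits in a mixed model:** say which enter. Table 4 makes week 8 a telephone contact with no ESR or CRP, so how DAS28 is obtained then needs stating.
- **Key secondary:** remission (DAS28 below 2.6) at week 12, tested only if the primary is significant.
- **Supportive:** the repeated-measures ANOVA and its post hoc comparisons.

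The cost is a change of wording and routine code in R, which the plan already uses. No new data, visits or patients are needed.

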骨碎补	Gu Suibu	*Drynaria roosii* Nakaike	Polypodiaceae	Dried rhizome	147	5.292
桂枝	Gui Zhi	*Neolitsea cassia* (L.) Kosterm.	Lauraceae	Dried young branch	98	3.528
淫羊藿	Yin Yanghuo	*Epimedium sagittatum* (Siebold & Zucc.) Maxim.	Berberidaceae	Dried aerial parts	147	5.292
防风	Fang Feng	*Saposhnikovia divaricata* (Turcz. ex Ledeb.) Schischk.	Apiaceae	Dried root	98	3.528
威灵仙	Wei Lingxian	*Clematis chinensis* Osbeck	Ranunculaceae	Dried root and rhizome	147	5.292
白芍	Bai Shao	*Paeonia lactiflora* Pall.	Paeoniaceae	Dried root	117.67	4.236
狗脊	Gou Ji	*Cibotium barometz* (L.) J.Sm.	Cyatheaceae	Dried rhizome	147	5.292
皂角刺	Zao Jiao Ci	*Gleditsia sinensis* Lam.	Fabaceae	Dried spine	98	3.528
知母	Zhi Mu	*Anemarrhena asphodeloides* Bunge	Asparagaceae	Dried rhizome	147	5.292
伸筋草	Shen Jincao	*Lycopodium japonicum* Thunb.	Lycopodiaceae	Dried herb	98	3.528
红花	Hong Hua	*Carthamus tinctorius* L.	Asteraceae	Dried flower	98	3.528
羊骨	Yang Gu	*Capra hircus* L.	Caprinae	Dried bone	196.44	7.072

Except for the experimental drugs, the participants are not allowed to use other botanical, zoological and Western medicines with immunosuppressive or immunomodulatory effects. All treatments that may improve RA, such as acupuncture and massage, will be banned during the trial. If a patient has special circumstances during the observation period, for instance. In that case, when pain is unbearable, drugs such as low-dose NSAIDs can be used in combination under the direction of the investigator, and all drug use outside the study protocol must be recorded in detail.

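### Re-running the comparison within subgroups formed by on-study NSAID use conditions on a post-randomisation, pain-driven variable and cannot verify the intention-to-treat result

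*Protocol article*

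**What the plan says.** The Statistical analysis section gives the primary comparison of DAS28 on the intention-to-treat principle. It then introduces a further layer: "Sensitivity analysis will be an essential part of the statistical analysis process to complement the interpretation of the results". As its content, and depending on how the data turn out, "the full samples will be divided into subgroups based on information about additional drugs (e.g. NSAIDs" being the named example. The list continues with "co-existing underlying conditions (e.g. hypertension, diabetes), long-term use of other drugs, etc". The purpose is explicit: "The calculations will be re-run in each subgroup to verify the validity of the results".

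The only text that governs NSAID use in this trial is under Interventions. It begins "If a patient has special circumstances during the observation period" and goes on: "when pain is unbearable, drugs such as low-dose NSAIDs can be used in combination under the direction of the investigator". Drug use outside the protocol has to be recorded in detail.

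Pain is also measured as an outcome. The Outcomes section lists the "visual analogue scale for pain (VAS") as secondary, and Table 3 makes the patient's assessment of pain one of the ACR50 components.

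**The concern.** A sensitivity analysis should vary an assumption of the primary analysis and show whether the answer moves. Splitting the sample by on-study NSAID use does not do that. It replaces one randomised comparison with two non-randomised ones.

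If Wangbi granule relieves pain, as the trial hopes, NSAID users on active treatment are those who did badly despite it, while users on placebo are a less selected group. The same selection, in mirror image, operates among non-users. Each within-subgroup contrast then mixes the treatment effect with a difference in the kind of patient being compared.

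What is at stake is interpretation. A correct primary result could be reported as not confirmed, because both subgroups show a smaller effect than the whole sample. Agreement would reassure no better, since it too comes from comparisons that randomisation does not protect.

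**Working it through.** **Step 1: what kind of variable is it?** Setting the sections side by side:

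- Timing: Interventions places this NSAID use in the observation period, so after randomisation.
- Trigger: unbearable pain, at the investigator's direction.
- Link to outcome: pain is a secondary outcome and an ACR50 component.
- Baseline reading: the Statistical analysis section lists long-term use of other drugs as a separate factor, and nothing limits the additional-drug split to use before randomisation.

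The natural reading is a post-randomisation variable driven by an outcome.

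**Step 2: can a uniform effect be distorted?** The article states no figure to reproduce here, so this is an illustration. The −0.50 effect is the difference named under Sample size calculation. Everything else is assumed:

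- On-treatment score: y = 3.0 − 0.5 × arm + SD × u, with u standard normal and SD 0.8, 1.0 or 1.57. The last is back-solved from 155 per group, because no SD is stated: 0.5 × √(155/2) ÷ (1.960 + 0.842) = 1.57.
- NSAID use: logit P(use) = −1 + slope × (y − 3.0)/SD, with disease activity standing in for pain.
- NSAIDs have no effect of their own on DAS28.
- 2,000,000 simulated patients per scenario.

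| Link (slope per SD) | Whole sample | Users | Non-users | Attenuation |
|---|---|---|---|---|
| none (0) | −0.50 | about −0.50 | about −0.50 | none |
| weak (0.5) | −0.50 | about −0.48 | about −0.48 | 1 − 0.48/0.50 = 4% |
| moderate (1) | −0.50 | about −0.42 | −0.43 to −0.44 | 12% to 16% |
| strong (2) | −0.50 | about −0.30 | −0.35 to −0.36 | 28% to 40% |

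With no treatment effect, the same model gives no subgroup bias at any slope.

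**Step 3: where does the missing effect go?** Take slope 1, SD 1.0. NSAID use is 22.1% on active and 30.3% on control; the subgroup effects are −0.415 and −0.436. Weighted by the active arm's mix:

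0.221 × (−0.415) + 0.779 × (−0.436) = −0.431.

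The whole-sample effect is −0.500, so −0.069 is unaccounted for. It lies in the shift of patients from users to non-users, 0.221 − 0.303 = −0.082, multiplied by the control-arm gap between users and non-users. That gap is therefore about 0.069/0.082 = 0.84 points. The subgroup analysis cannot show this part of the benefit.

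**Step 4: a hard trigger.** Now suppose NSAIDs start when an interim DAS28 exceeds 3.2 or 3.5, with baseline uniform on 2.6 to 3.2, SD 0.8, and an interim score carrying 0.7 of the patient's deviation and of the effect. The result depends strongly on the assumed noise in the interim score:

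- Noise SD 0.4: −0.23 to −0.25 in users and −0.34 to −0.39 in non-users, an attenuation of 1 − 0.39/0.50 = 22% to 1 − 0.23/0.50 = 54%.
- Noise SD 1.0: about −0.41 in users and −0.43 to −0.44 in non-users, close to the moderate logistic case.

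The article supports no particular trigger or noise level.

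**The case against.** The best defence is that additional drugs might mean NSAIDs already taken at entry, since Table 1 does not exclude them. That is possible. But long-term drugs are listed separately, and the only text on NSAID use concerns the observation period. If baseline use was meant, the wording still needs to say so.

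Several limits on the point do stand.

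- **Size.** A reader might infer from the hard-threshold model that both subgroups will understate the effect by a fifth to a half. The documents give no SD, no NSAID rate and no DAS28 trigger, and other reasonable assumptions give anything from no attenuation upward. The right word is can, not will.
- **False positives.** A reader might also infer that the split would create a spurious subgroup effect. The mechanism shown here does not: without a treatment effect, the logistic model produces no bias. Such a risk would have to come from multiplicity, which was not assessed.
- **Primary result.** The primary comparison is by intention to treat in everyone, and no stated rule lets a subgroup overturn it.
- **Other subgroups.** The criticism does not reach co-existing conditions or long-term drugs if these are fixed at baseline. They are acceptable as exploratory analyses.
- **Analysis detail.** Interaction tests and strategies for intercurrent events may be left to an analysis plan that is not shown, so their absence is not the fault. The fault is the split, and the purpose given for it, that the article itself fixes.

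**Conclusion.** The point holds for subgroups defined by drug use during the trial, and for the claim that re-running the comparison in them verifies the result. These are not randomised comparisons, whatever they show.

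The direction of distortion in the models is towards zero in both subgroups. It arises when treatment changes pain or NSAID use. Its size ranges from nothing through 12% to 16% at a moderate link and 28% to 40% at a strong one, and can exceed that under a tight hard threshold. All of this assumes that NSAIDs do not themselves change DAS28, and that disease activity is a fair stand-in for pain.

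The documents do not support reading this as a flaw in the primary intention-to-treat analysis. The correction should be made because the article calls this layer of analysis essential to interpretation, and as written it could mislead.

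**What to change.** - **Subgroups.** Restrict them to factors recorded before randomisation, including baseline NSAID use, co-existing conditions and long-term drugs. Name them in advance, label them exploratory, and report a treatment-by-factor interaction with its confidence interval. Delete the stated purpose of verifying validity.
- **On-study NSAID use.** Examine it in the full randomised set. State that the primary analysis keeps all participants regardless of NSAID use. Add a sensitivity analysis that treats DAS28 after NSAID start as missing and imputes it, or one that counts NSAID users as not in remission. If imputation is chosen, say how it fits with the existing rule that limits multiple imputation to variables with no more than 20% missing; the assumed NSAID rates above would pass that limit in several scenarios.
- **Consistency.** Reconcile Interventions, which allows NSAIDs with recording, with Safety, which says that termination should be considered when other medications associated with improvement of RA are required, and treats such participants as off-cases. The two sections must make clear whether on-study NSAID users stay in the trial, because that determines what data any of these analyses can use.

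The cost is wording. On-study drug use is already to be recorded; the team should confirm that the case report form also captures NSAID use at baseline and the NSAID start date.
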